**Interventions**

Therapeutic effect of probiotics and synbiotics on the serum level of thyroid hormones have been assessed with different species and doses of bacteria and follow-up duration between 4 to 12 weeks (30, 31). Previous trials have used either different species of Lactobacillus genus (32) or a combination of Lactobacillus and Bifidobacterium (21, 29-31, 33). The microbial load of the supplements varied between 10^7^ to 10^10^ CFU/g. Inulin, fructo-, and/or galacto- oligosaccharide have been used as the prebiotic component of synbiotic (21, 30, 32). We decided to conduct this intervention with synbiotic instead of probiotic, since the synergistic interaction of probiotic and prebiotic can more effectively improve the microbial composition of the gut and maintain the intestinal microbial balance (10). The duration of intervention was decided to be 10 weeks, as the previous trials with less duration of intervention reported no significant effect of synbiotic or probiotics on serum level of thyroid hormones and BP (29, 33). A comprehensive meta-analysis also showed that less than 8 weeks supplementation with probiotics had no significant effect on BP (34). The synbiotic supplement (Familact, 500 mg) that will be used in this study contains Lactobacillus casei, Lactobacillus acidophilus, Lactobacillus rhamnus, Lactobacillus bulgaricus, Bifidobacterium Breve, Bifidobacterium Longum, Streptococcus thermophilus plus fructo-oligosaccharide with microbial population of 10^9^ CFU/g. Placebos contain lactose, magnesium stearate, talc, and silicon dioxide and will be made in the same shape, color, odor and taste as the synbiotic supplements. Zist-takhmir Pharmacutical company will provide the synbiotic and placebo capsules. All participants will receive a capsule (Synbiotic supplement or placebo) to be consumed with lunch, daily. Also, the participants will receive appropriate recommendations regarding diet and PA. The recommendations will include: to follow a hypo-caloric diet; to avoid excessive intake of high-fat products (whole dairy products, poultry fat (the skin on chicken), processed meat, butter, cream, ice cream, and palm oil); to avoid excessive sugar intake (candy, soda, syrups, sugar-loaded desserts, caramels, chocolate); to increase PA by walking or cycling for at least 20 minutes for at least 5 days a week.

The supplements will be delivered to the participants at the first appointment and the supplement boxes will be collected at the end of the intervention by the outcome assessor. To recall the participants of the supplements intake and follow the routine recommendations, we will use telephone or online applications such as WhatsApp or Telegram. If supplements intake is missed at lunch, patients will be advised to take them during the same day. They will also be asked to report any complications or adverse event during the study period. The intervention will be discontinued in case of severe and serious complications following the supplementation.

**Outcomes**

Schedule of outcome assessment is represented in Figure 2. The primary outcomes include serum levels of TSH and fT4. The secondary outcomes are BP, quality of life, and depression. The information on anthropometric indices, PA, and dietary intake will be collected to control the potential confounders and covariates. The primary and secondary outcomes will be conducted at baseline and the end of the study (10th week) for all participants and change from baseline will be reported. Adherence will be checked every week.

**Figure 1**. Flow chart of the study design.

Eligible hypothyroid adults (women/men) with written informed consent will be recruited from Baqiyatallah hospital and will be enrolled in this RCT (n=56)

Randomize to two parallel treatment groups for 10 weeks (70 days):

1) synbiotic supplement (n= 28)

2) placebo (n= 28)

1

**Baseline information:**

Demographic and Anthropometric information, medical history, physical activity (IPAQ), dietary intake (3-day food record). Laboratory investigations of thyroid hormones, SBP & DBP, quality of life (SF-36), depression (Beck questionnaire).

**Follow-up:**

Every week by telephone or through social media (telegram or WhatsApp) for the recall of: 1) taking the supplements, 2) tracking possible complications following supplement intake, and 3) Emphasis on maintaining the routine diet and physical activity.

**Final assessment:**

Demographic and Anthropometric information, medical history, physical activity (IPAQ), dietary intake (3-day food record). Laboratory investigations of thyroid hormones, SBP & DBP, quality of life (SF-36), depression (Beck questionnaire), and pill counts.

Statistical Analysis

*RCT: randomized controlled trial; IPAQ: International Physical Activity Questionnaire; SF- 36: short form-36 questionnaire for quality of life, SBP: Systolic Blood Pressure; DBP: Diastolic Blood Pressure.*

**Participant timeline**

**Figure 2**. Schedule of enrolment, interventions, and assessments.

|  | **STUDY PERIOD** | | | | | |
| --- | --- | --- | --- | --- | --- | --- |
|  | **Enrolment** | **Allocation** | **Post-allocation** | | | **Close-out** |
| **TIMEPOINT**** | ***Day 0*** | ***Day 0*** | ***M1*** | ***M2*** | ***W10*** | ***W10-W11*** |
| **ENROLMENT:** |  | | | | | |
| ***Eligibility screen*** | X |  |  |  |  |  |
| ***Informed consent*** | X |  |  |  |  |  |
| ***Allocation*** |  | X |  |  |  |  |
| **INTERVENTIONS:** |  | | | | | |
| ***Synbiotic group*** |  |  |  |  |  |  |
| ***Placebo group*** |  |  |  |  |  |  |
| **ASSESSMENTS:** |  | | | | | |
| ***Demographic and Anthropometric Data (age, weight, height, WC, BMI, PA, dietary energy and macronutrient intake, education, career, marital status, duration of the disease, dose of levothyroxine, and type of hypothyroidism)*** | X | X |  |  | X |  |
| ***Primary Outcomes (FT4 and TSH)*** | X | X |  |  | X |  |
| ***Secondary Outcomes (SBP, DBP, depression, and quality of life*** | X | X |  |  | X |  |
| ***Participant Adherence*** |  |  |  |  | X |  |
| ***Adverse Events*** |  |  |  |  | X |  |

***List of specific timepoints.*

*W: week; M: month; WC: waist circumstance; BMI: body mass index; PA: physical activity; FT4: thyroxine; TSH: thyroid stimulating hormone; SBP: systolic blood pressure; DBP: diastolic blood pressure.*

**Sample size**

The sample size was calculated with G-power software version 3.1.9.2. To calculate the sample size, the study of Talebi et al. (29) was used, which was an 8-week clinical trial with two parallel groups. The sample size was calculated considering the probability of the first type error equal to 0.05 (α = 0.05, significance), and the probability of the second type error equal to 0.80 (β = 0.2, power). In this study, the mean change ± standard deviation of placebo and synbiotic groups regarding TSH levels after 8 weeks of intervention were 0.08 ± 0.09 mIU/L and 0.028 ± 0.09 mIU/L, respectively. In this study, in order to observe 0.28 mIU/L difference in serum TSH levels between the two groups at the end of the study, a sample size of 24 patients in each group is required. According to an expected 15% loss to follow-up, the final sample size included in each group will be 28 patients.

[figure not shown]

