**Eligibility criteria**

Inclusion criteria

Women or men (25-55 years old) with subclinical hypothyroidism (elevated TSH level and a normal or low free T4 level) for at least a year, and BMI less than 35 who are being treated by levothyroxine. Voluntary written informed consent for all patients is mandatory before any study related procedures.

Exclusionary criteria

The participants must not have any of the following: lactating or pregnant; History of taking probiotic or synbiotic supplements in the last three months; Smoking or alcohol consumption; Taking appetite suppressants such as antibiotics; Use of antibiotics and any medications that interact with synbiotics; Gastrointestinal diseases such as stomach ulcers, diarrhea or constipation etc. for three months before or during the intervention; unwillingness to continue cooperation, non-compliance during the intervention, or no signed informed consent. Participants will also be excluded in case of providing incomplete questionnaires (more than 40% of the dietary questionnaire is incomplete), catching infectious diseases such as Covid-19 during the study, occurrence of pregnancy, undergoing surgery, occurrence of a change in the dose or type of medication, consumption of foods enriched with probiotics (e.g. probiotic yoghurt) during the study.

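### The 80% power claim rests on an SD of TSH change of 0.09 mIU/L that is not shown to apply to the patients enrolled; with 24 per group it holds for 0.28 mIU/L only if that SD is about 0.34 or less

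*Protocol*

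**What the plan says.** The Sample size section relies on one earlier 8-week synbiotic trial (reference 29). It labels the figures as mean change ± standard deviation and gives them, placebo first, as "regarding TSH levels after 8 weeks of intervention were 0.08 ± 0.09 mIU/L and 0.028 ± 0.09 mIU/L". The target is set "in order to observe 0.28 mIU/L difference in serum TSH levels between the two groups at the end of the study". Alpha is 0.05. For the other error rate the section has "the probability of the second type error equal to 0.80 (β = 0.2, power", which I read as power 0.80. The result is that "a sample size of 24 patients in each group is required", and then: "According to an expected 15% loss to follow-up, the final sample size included in each group will be 28 patients".

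Three other sections bear on whether 0.09 carries over:

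- Eligibility criteria describes the population as having "subclinical hypothyroidism (elevated TSH level and a normal or low free T4 level) for at least a year", on levothyroxine and with BMI below 35. It gives no numeric TSH limit.
- Laboratory investigations plans a fasting blood sample at baseline and at the end of the study, with TSH measured by an ELISA kit. No assay precision is given.
- Interventions justifies the 10-week duration by saying that "previous trials with less duration of intervention reported no significant effect of synbiotic or probiotics on serum level of thyroid hormones" and on blood pressure, citing reference 29 and one other trial.

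**The concern.** The SD of individual change is the input that fixes what a trial of this size can detect. Here it comes from a single trial of different duration, and the Protocol does not argue that it fits the patients, assay or interval of this one. The value is also very small against any elevated TSH. A TSH change is the difference of two measured values, so its SD contains both within-person fluctuation and assay error, each counted twice.

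The Protocol claims 80% power for 0.28 mIU/L on a primary outcome. If the true SD is well above 0.09, a non-significant result could be read as evidence against a 0.28 mIU/L effect when the trial had little chance of showing one. Making the section's figures agree with one another would not remove this, because the SD would still need a justification.

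**Working it through.** **Inputs from the Protocol.** Mean changes 0.08 and 0.028 mIU/L, so a difference of 0.08 − 0.028 = 0.052; SD 0.09; target difference 0.28; alpha 0.05 (two-sided assumed, as sidedness is not stated); power 0.80; 24 evaluable per group. All power figures use the two-sample t-test (noncentral t).

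**Step 1: the plan's own figure.** It does not follow from the quoted inputs.

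- Difference 0.28, SD 0.09: standardised difference 0.28/0.09 = 3.11, which needs about 3 per group.
- Difference 0.052, SD 0.09: standardised difference 0.578, which needs about 48 per group. With 24 per group, power is about 50%.

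So no quoted combination of difference and SD supports 24 per group.

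**Step 2: what 24 per group can support.** Power of 80% needs a standardised difference of 0.826. For 0.28 mIU/L the SD may therefore be at most 0.28/0.826 = 0.339, or 3.8 times the quoted 0.09.

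**Step 3: what an SD of 0.09 implies.** Take SD of change = √2 × CV × TSH, where CV combines within-person and assay variation. This leaves out real differences between patients in their change, which would add to the SD. Then CV = SD/(√2 × TSH). The TSH levels are assumed.

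| Assumed TSH (mIU/L) | CV implied by SD 0.09 | CV implied by SD 0.339 |
|---|---|---|
| 4 | 1.6% | 6.0% |
| 4.5 | 1.4% | 5.3% |
| 6 | 1.1% | 4.0% |
| 10 | 0.6% | 2.4% |

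**Step 4: could ±0.09 be a standard error?** Interventions lists reference 29 among trials without a significant effect. For a difference of 0.052 with SD 0.09 in each arm, t = 0.052/(0.09 × √(2/n)):

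- n = 24 per arm: P = 0.051
- n = 25: P = 0.047
- n = 30: P = 0.029

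Read as an SD, ±0.09 fits a null TSH result only with 24 or fewer per arm. Read as a standard error, t = 0.052/(√2 × 0.09) = 0.41, far from significance at any arm size. The source trial's arm size is not in the Protocol. If it is a standard error, SD = 0.09 × √n: 0.40 at n = 20, 0.45 at n = 25, 0.53 at n = 35 (arm sizes assumed).

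**Step 5: power for 0.28 mIU/L with 24 per group, over assumed SDs.**

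| SD of change | Where it comes from | Power for 0.28 | Detectable at 80% (0.826 × SD) |
|---|---|---|---|
| 0.32 | TSH 4.5, CV 5% | 85% | 0.26 |
| 0.34 | limit from step 2 | 80% | 0.28 |
| 0.40 | standard error, n = 20 | 66% | 0.33 |
| 0.45 | standard error, n = 25 | 56% | 0.37 |
| 0.53 | standard error, n = 35 | 43% | 0.44 |
| 0.64 | TSH 4.5, CV 10% | 32% | 0.53 |

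If the section were repaired the other way, to 0.052 with 48 per group, there would be no slack: power is about 81% at SD 0.09 and about 40% at SD 0.15 (both by normal approximation).

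**The case against.** A reader might infer from these figures that 80% power is certainly not delivered, or that the detectable difference is two to four times 0.28 mIU/L. The Protocol supports neither. It gives no baseline TSH, no assay or biological CV, and no SD of TSH change other than 0.09. The standard-error reading gives 0.33 to 0.44 mIU/L, only 1.2 to 1.6 times 0.28, and the most favourable row above still exceeds 80% power.

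Four further objections have weight.

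- **Eligibility can be read less strictly.** The parenthesis may define the diagnosis of patients now under treatment, with no TSH cut-off at entry. By the same formula, TSH 2.0 with CV 10% gives SD 0.28 and 92% power; TSH 3.0 with CV 7% gives SD 0.30 and 89%. These values are also assumed. Even so, an SD of 0.09 would need a CV of 3.2% at TSH 2 and 2.1% at TSH 3, so the quoted SD still needs justifying.
- **Adjustment helps.** Statistical methods plans ANCOVA for confounders, though it does not name baseline TSH as a covariate. Such adjustment could at best halve the variance. At TSH 4.5 that best case gives 85% power with CV 7%, but about 56% with CV 10% (SD 0.64/√2 = 0.45).
- **The standard-error argument is conditional.** The section labels the figure a standard deviation. The sentence in Interventions pools two trials and several outcomes and does not report reference 29's TSH test. This is a reason to check the source, not proof of an error.
- **A figure after the Sample size section is not shown** and may hold the calculation inputs. It could explain the 24, but the text would still quote 0.09.

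What stands is that the SD is unjustified for this trial and that 80% power depends on a condition the Protocol does not state.

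**Conclusion.** The point holds as a failure to justify the planning SD. The stated 80% power for 0.28 mIU/L is unsupported: the quoted SD does not lead to 24 per group, and the SD that would (about 0.34) appears nowhere in the text. That an SD of 0.09 is implausibly small for elevated TSH is my judgement, resting on the assumed TSH range of 4 to 10 mIU/L and the simple CV formula; the implied CV of 0.6% to 1.6% has to cover biological and assay variation together. Loss of power is a risk whose size depends on the true SD: none up to about 0.34, then 66%, 43% and 32% power at assumed SDs of 0.40, 0.53 and 0.64. This affects how a null primary result can be read, and should be corrected.

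**What to change.** In the Sample size section:

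1. Check in the source trial whether ±0.09 is an SD or a standard error, and say which.
2. Adopt an SD of TSH change justified for levothyroxine-treated patients with elevated TSH, measured with this assay about 10 weeks apart.
3. Keep 28 per group and replace the present power claim with wording such as: *24 evaluable patients per group give 80% power (two-sided 0.05) for a difference of 0.83 SD of TSH change.* Give the mIU/L value at the adopted SD and at one higher SD.
4. State that a null result does not exclude smaller differences.

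This is a change of wording and needs no extra patients, visits or assays. The price is that the stated detectable difference will probably look less favourable.

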**Statistical methods**

Before statistical analysis, all data will be reviewed in terms of accuracy and completeness. Data will be analyzed using SPSS software (IBM Corp. Released 2016. IBM SPSS Statistics for Windows, Version 24.0. Armonk, NY: IBM Corp). For all analyses, a P value < 0.05 will be considered statistically significant. The normality of data will be checked by the Shapiro-Wilk W Test, P-P and Q-Q plots. All variables will be reported as mean ± SD for before, after the intervention and changes (after minus before). Baseline characteristics of quantitative biochemical and demographic variables will be compared between the two groups by independent sample t-test. The difference between the two groups regarding qualitative variables will be assessed by Chi-square test. Analysis of Covariance (ANCOVA) will be performed to eliminate the effect of confounders. Changes from the base-line to post-intervention within the groups will be illustrated through a paired t-test or Wilcoxon signed-rank test. GraphPad Prism software will be used to draw graphs and illustrate the results (GraphPad Prism version 8.0.0 for Windows, GraphPad Software, San Diego, California USA, [www.graphpad.com](http://www.graphpad.com)).

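### The stated inputs do not give 24 per group at 80% power: the quoted TSH changes need 49 per group, and the stated target of 0.28 mIU/L needs only 3

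*Protocol*

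**What the plan says.** The Sample size section of the protocol bases the calculation on an earlier 8-week, two-arm synbiotic trial (reference 29) and names G*Power as the software. It sets a significance level of 5%. Its entry for power reads: "the probability of the second type error equal to 0.80 (β = 0.2, power"). This wording calls 0.80 an error probability, but the β of 0.2 in the bracket makes clear that 80% power is meant.

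The mean TSH changes for placebo and synbiotic are given as "0.08 ± 0.09 mIU/L and 0.028 ± 0.09 mIU/L, respectively". The target is then set: "in order to observe 0.28 mIU/L difference in serum TSH levels between the two groups at the end of the study". The conclusion is that "a sample size of 24 patients in each group is required". Allowing for 15% loss, "the final sample size included in each group will be 28 patients".

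The number of sides is not given. The Statistical methods section adds only a threshold: "For all analyses, a P value < 0.05 will be considered statistically significant". TSH is one of the two primary outcomes, and the total of 56 is repeated in the study flow chart and under Recruitment.

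**The concern.** Two successive sentences of one paragraph disagree. The quoted mean changes differ by 0.08 − 0.028 = 0.052 mIU/L, yet the planned difference is 0.28 mIU/L. No second SD is offered for the larger figure, so the reader cannot tell which effect size led to 24. The inputs are also changes from baseline, while the target is worded as a difference between groups at the end of the study.

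This is the only justification for the size of the trial. If the quoted means and SDs are right, a true effect of that size would be missed about half the time, and a null TSH result would not carry the weight that 80% power implies. If 0.28 with SD 0.09 is right, the trial is several times larger than its own calculation requires. The document does not show which applies.

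**Working it through.** **Inputs (protocol, Sample size):** α = 0.05; power 0.80; changes 0.08 and 0.028 mIU/L; SD 0.09 in each group; stated target 0.28 mIU/L; stated n = 24 per group, 28 after 15% loss; equal allocation. Two-sided testing is assumed because the number of sides is not stated; one-sided results are given as well.

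**Method.** Standardised difference d = Δ/SD. For a two-sample t-test with n per group, the noncentrality is d√(n/2) on 2n − 2 degrees of freedom. The normal approximation is n = 2(1.960 + 0.842)²/d² = 15.70/d².

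**Attempt 1: the quoted means.**
- d = 0.052/0.09 = 0.578.
- Normal approximation: 15.70/0.334 = 47.02, so 48 per group.
- Noncentral t: 49 per group (48 falls a hair short of 80%).
- At n = 24: noncentrality 0.578 × √12 = 2.00, against a critical t of 2.01 on 46 df, so power is 50.0%.
- At n = 28 (no losses at all): 56.5%.
- With 15% loss, 49 evaluable means 49/0.85 = 57.6, so 58 enrolled per group.

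**Attempt 2: the stated target.**
- d = 0.28/0.09 = 3.11.
- Normal approximation: 15.70/9.68 = 1.62, so 2 per group.
- Noncentral t: 3 per group (power 81%). At 24 per group, power is essentially 100%.

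**Other readings at 80% power, SD 0.09, t-test:**

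| Reading | Δ (mIU/L) | n per group, two-sided | n per group, one-sided |
|---|---|---|---|
| As quoted | 0.052 | 49 | 38 |
| Sign of 0.028 reversed | 0.108 | 12 | 10 |
| Placebo change alone | 0.08 | 21 | 17 |
| Synbiotic change alone | 0.028 | 164 | 129 |
| 0.028 read as 0.28 | 0.20 | 5 | 4 |
| Stated target | 0.28 | 3 | 3 |
| 0.028 read as −0.28 | 0.36 | 3 | 2 |

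None gives 24. One-sided testing with the quoted means still has only 63% power at 24. The nearest match found was Δ = 0.08, one-sided, at 90% power (23 per group). It contradicts the stated 80% and ignores the synbiotic change.

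**Working backwards from 24.** Two-sided 80% power at n = 24 needs d = 0.826. That corresponds to:
- Δ = 0.826 × 0.09 = 0.074 mIU/L if the SD is 0.09;
- SD = 0.28/0.826 = 0.34 if the difference is 0.28;
- SD = 0.052/0.826 = 0.063 if the difference is 0.052.

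None of these values appears in the readable text.

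**Attrition step.** 24/0.85 = 28.2, while 28 × 0.85 = 23.8. Strictly this calls for 29, but the shortfall is a fraction of one patient.

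**The case against.** *A figure follows the Sample size text and is not reproduced in the copy reviewed.* It may show the software output, including an SD or effect size that leads to 24. That is possible, so the finding is limited to the readable text. But no figure can make 0.052 equal 0.28, and the printed paragraph would still need correcting.

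*The 50% power figure depends on which input is right.* This stands. It applies if 0.052 with SD 0.09 is the effect of interest. With 0.28 and SD 0.09 the trial would be far larger than needed. What is shown is that the stated power cannot be verified and that the quoted means do not support it, not that the trial's true power is 50%.

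*The analysis plans ANCOVA, which can reduce the residual variance.* Going from 49 to 24 per group would need covariates explaining 1 − 24/49 = 51% of the variance, a correlation of about 0.71. The Sample size section claims no such gain, so this does not rescue the figure.

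*End-of-study levels and changes have the same expected between-group difference under randomisation.* This is true. The SDs differ, however, and the only SD given is for change. The mixed wording is secondary.

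*Planning from a trial with a non-significant result is not an arithmetic error.* Agreed. The Interventions section cites reference 29 among shorter trials without a significant effect and uses this to justify 10 weeks. That is a reason to explain the planned difference, but it does not carry the finding. The attrition rounding does not carry it either.

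**Conclusion.** The concern holds. The planned difference of 0.28 mIU/L is not the difference between the quoted mean changes (0.052 mIU/L), and neither gives 24 per group at 80% power: the first needs 3 and the second needs 49. On the quoted means and SDs, power is 50% with 24 evaluable per group and 56% with all 28.

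These figures assume a two-sided 5% unadjusted two-sample t-test with a common SD of 0.09. One-sided testing changes 49 to 38 and leaves 3 unchanged. Whether 0.28, 0.028 or 0.09 is a misprint cannot be settled from the protocol. Since this is the only power statement and it determines enrolment, it must be corrected.

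**What to change.** Check the transcribed means and SDs against the source trial. Then rewrite the Sample size paragraph so that it states one planned difference in TSH change with its rationale, one SD for change, the number of sides, the test, any ANCOVA gain that is claimed, and the n that follows. Describe 0.80 as power rather than as an error probability, and tidy the attrition step.

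If enrolment stays at 56, state what it delivers. With 24 evaluable per group, power is 80% for a difference of 0.83 SD (0.074 mIU/L if the SD is 0.09), and about 50% for 0.052 mIU/L with SD 0.09. Any null TSH result should be read against that figure.

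The cost is one rewritten paragraph. No extra patients are needed, but unless the source check changes the inputs, the stated power becomes less favourable.

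### The 15% allowance is labelled loss to follow-up, but the protocol also removes randomised participants for other reasons; if these come on top, fewer than 24 per group remain

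*Protocol*

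**What the plan says.** The Sample size section of the protocol states that "a sample size of 24 patients in each group is required" and then allows for attrition: "According to an expected 15% loss to follow-up, the final sample size included in each group will be 28 patients". The flow chart (Figure 1) and the Recruitment section agree on 56 in total.

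The exclusionary criteria, under Eligibility criteria, mix conditions that apply at entry with events that can only happen after it. The later events include "catching infectious diseases such as Covid-19 during the study, occurrence of pregnancy, undergoing surgery, occurrence of a change in the dose or type of medication". The same paragraph adds eating probiotic-enriched foods during the study, non-compliance, unwillingness to continue, gastrointestinal disease arising during the intervention, and a dietary questionnaire that is more than 40% incomplete. No expected rate is given for any of these. The Sample size section does not mention them.

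**The concern.** An attrition allowance does its job only if it covers every route by which a randomised participant ends up without an analysed outcome. Here the allowance is named after one route, loss to follow-up, while another section creates several more by rule. A participant who catches an infection, has a levothyroxine dose changed or eats probiotic yoghurt is normally still in contact and able to give blood at week 10.

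Some of these events are plausible on the protocol's own facts. It is dated October 2021 and names Covid-19. Its background lists constipation as a manifestation of hypothyroidism, and constipation during the intervention is a ground for exclusion. All participants take levothyroxine, so any change in its dose counts.

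Two things are at stake. One is the number evaluable, and with it the power. The other is the comparison itself: non-compliance, bowel symptoms and medication changes occur after randomisation and may be related to treatment or to the outcome, so removing those participants can leave two groups that are no longer comparable.

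**Working it through.** **Inputs from the Sample size section:** 24 per group required; 15% expected loss; 28 per group recruited; α = 0.05; power 0.80 (β = 0.2). Sidedness is not stated; a two-sided t-test is assumed.

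**Input not in the protocol:** the rate of the rule-based removals. Values of 5%, 10% and 20% of those remaining after the 15% loss are assumed, to show a range.

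**1. The plan's own figure.** 24 / (1 − 0.15) = 28.24, which is 28 to the nearest whole number. 24 × 1.15 = 27.6 also gives 28 when rounded up. So the stated 28 reproduces.

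**2. What 28 delivers at 15%.** 28 × 0.85 = 23.8. In whole patients, losing 4 of 28 (14.3%) leaves 24 and losing 5 (17.9%) leaves 23.

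**3. Reference effect.** The standardised difference at which 24 per group gives exactly 80% power is d = 0.826. It is used only as a yardstick, solved back from the stated 24. At that d, power is 79.7% with 23.8 per group and 78.2% with 23.

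**4. Removals on top of the 15%.** Remaining per group = 28 × 0.85 × (1 − r):

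| Further removal r (assumed) | Remaining per group | Power at d = 0.826 | Recruits per group to keep 24: 24 / [0.85 × (1 − r)] |
| --- | --- | --- | --- |
| 0% | 23.8 | 79.7% | 28.2 |
| 5% | 22.6 | 77.5% | 29.7 |
| 10% | 21.4 | 75.2% | 31.4 |
| 20% | 19.0 | 69.9% | 35.3 |

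**5. The two sections side by side.** If the removals fall outside the 15%, the allowance is too small by an amount that the protocol does not estimate. If they fall inside it, the label is wrong and true loss to follow-up is being assumed lower than 15%. The Sample size section needs rewording either way.

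**The case against.** The strongest reply is that the protocol never says the removals are left out of the 15%. Planners often use loss to follow-up loosely for all attrition, and one listed reason, unwillingness to continue, is ordinary loss to follow-up, so the two sets overlap. This stands: that the removals are additional is a possible reading, not a stated fact. The 5% to 20% rates are assumptions, and the power losses beyond step 3 depend on them entirely.

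A reader might also infer that the inflation is simply miscalculated and that 29 per group is needed, since 24 / 0.85 rounds up to 29. The documents do not support making that the point. The protocol gives no inflation formula, 28 is the nearest whole number to 28.24, and the gap is 0.2 of a patient, or 0.3 points of power. Nor does 29 secure 24. With 15% independent loss, the chance of keeping at least 24 is 59% in one arm and 34% in both with 28 recruited; with 29 it is still only 74% and 54%. Most of that shortfall is sampling variation, which any inflation to an expected count leaves in place.

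A further objection is that the 24 is itself unsound, so power quoted against it has no firm base. That is fair. The section reports TSH changes that "were 0.08 ± 0.09 mIU/L and 0.028 ± 0.09 mIU/L, respectively", a difference of 0.08 − 0.028 = 0.052, yet sizes the trial "in order to observe 0.28 mIU/L difference in serum TSH levels between the two groups". With SD 0.09, a difference of 0.052 needs about 48 per group and 0.28 needs 2 to 3; neither gives 24. That is a separate and larger problem. It does not remove this one, because whatever number replaces 24 will need an allowance whose coverage is defined.

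Finally, the protocol does not say whether an excluded participant leaves treatment, follow-up or only the analysis, and a statistical analysis plan may define the analysis set. It could not recover week-10 samples that were never taken, so the protocol should settle collection.

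**Conclusion.** The point holds as a mismatch between two sections, not as an arithmetic error. The allowance is described as loss to follow-up, while the exclusion rules remove other participants who could still be measured. If those removals are additional, 28 recruited leaves fewer than 24 per group: about 22.6 to 19.0 for assumed further removals of 5% to 20%, with power about 77.5% to 69.9% instead of 80%. If they are already inside the 15%, the number is right to within rounding and only the wording is wrong.

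The possible bias from removing people after randomisation does not depend on the assumed rates, although the documents give nothing from which to estimate its size or direction. All power figures are conditional on 24 per group giving 80%, which the protocol's inputs do not reproduce. This is worth changing because the remedy is cheap, not because the shortfall is proven.

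**What to change.** 1. **Eligibility criteria.** Separate entry criteria from events during the study. For the latter, state that they are recorded and reported by group and are not grounds for dropping outcome data. Take the week-10 TSH and FT4 sample from every randomised participant still willing, and analyse each in the assigned group. This concerns outcome collection and analysis only; whether the supplement continues after such an event is a clinical matter outside this point.

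2. **Sample size.** State that the 15% is all-cause missing week-10 outcome, and that 28 per group leaves about 24 (24 if 4 are lost, 23 if 5 are lost). Carry the same definition over when the derivation of the 24 is redone.

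The cost is a few sentences and a few more week-10 samples. No extra patients are needed for this point. The downside is some dilution of the effect, because participants who went off protocol stay in the comparison. A sensitivity analysis restricted to participants without such events can be reported alongside, labelled as such.
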